## Discussion

In this paper we described the design of our study into the effects and cost-effectiveness of laser Doppler imaging in Dutch burn care. This is the first randomised controlled study that analyses not only the accuracy, but also the effects and costs of the introduction of LDI in burn care. Strengths of our study are the extensive cost calculations (not only LDI costs are included) and the detailed analysis of the possible impact of the introduction of the LDI in terms of process changes, i. e. changes in diagnosis and therapy. A limitation of this study is that the cost calculations will be performed in Dutch burn centres only. Although the multicentre analysis improves the generalisability of the cost distribution, compared to a monocentre analysis, total cost and cost distribution in other countries are probably different [31].

Another limitation of this study is that it tests the effectiveness of the introduction of LDI, so there’s a possible learning effect in the study. In the first patients, professionals will less likely rely on LDI and adapt their therapy. As a result, differences between randomisation groups will probably be smaller, and subsequently our study underestimates the full effect of the introduction of LDI in burn care.

Next to a time effect, there will probably also be an effect of differences in study sites. The usual care differs between study sites; this can influence the results of the introduction of LDI in the burn centres. These possible differences will be studied by providing sub-analyses per burn centre.

This study will undoubtedly contribute to our knowledge about the use of LDI in burn care and will provide evidence on its cost-effectiveness. Inclusion of patients started in December 2011 and presentation of data will be expected at the end of 2013.

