### Sample size

A total of 57.5% of admitted burn patients in the Netherlands is treated conservatively (unpublished data, Dutch Burn Repository R3, 2011). The time to wound healing in patients without surgery is approximately 13 days, this will not change after the introduction of LDI. In the 42.5% of surgically treated patients we do expect an effect on wound healing time, because of an earlier operation. The mean time to first transplantation is 14.0 days post burn, the mean time to wound healing is 5 days after surgery [28], resulting in a mean time to wound healing of 19.0 days. The overall mean time to wound healing for all patients combined is 15.6 days ((57.5%*13+ 42.5%*19)/100).

Petrie et al. describe a reduction of 5.3 days in LOS in patients undergoing surgery, after the introduction of the LDI. As a result, in our population, an overall effect of 2.25 (57.5%* 5.3) days can be expected, with a standard deviation of 5 days. A 2-sided test with an α level of 0.05 and a β level of 0.20 (power 0.80) indicates a required total sample size of 190 patients. We expect a low drop out rate because of a short time to follow up to assess primary outcome (time to wound healing). With a 5% drop out we need a total sample size of 200.

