## Randomisation

Patients are randomly allocated to the group ‘new diagnostic strategy’ or the group ‘current diagnostic strategy’, on the day of the LDI scan. Stratification will be performed for the three different centers and the severity of the burns: total burned surface area ≤10% or >10%. A randomisation list is prepared for each stratum on the principle of random permuted blocks of patients, using a random number table [29]. The allocation sequence is concealed by using sequentially numbered, opaque sealed envelopes (SNOSE) prepared by the coordinating researcher ([name]) which are opened at day of LDI after having obtained informed consent, by one of the local researchers [30].

The care provider, outcome assessor and patients are blinded to the results of the LDI in the group ‘current diagnostic strategy’. However, they are not blinded to the group in which patients are randomised.

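### The plan studies differences between burn centres only by sub-analyses per centre, and separate within-centre tests do not test whether the effect of LDI differs between centres

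*Protocol article*

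**What the plan says.** The Discussion of the protocol article lists site differences among the study's limitations. It says that a site effect is probable and gives the reason: "The usual care differs between study sites; this can influence the results of the introduction of LDI in the burn centres". The next sentence is the whole of the planned response: "These possible differences will be studied by providing sub-analyses per burn centre".

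The Randomisation section shows that centre is built into the design: "Stratification will be performed for the three different centers and the severity of the burns". In the Statistical analysis section, time to wound healing is compared between the two strategies by Kaplan-Meier curves and a log-rank test. That section contains no regression model for healing time, no strategy-by-centre term and no test of heterogeneity, and none appears elsewhere in the article. The Sample size section is written for the overall comparison only.

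**The concern.** The question raised is about effect modification: does LDI change healing time more in one centre than in another? The method named is a separate analysis in each centre. If the primary method is simply repeated by centre, the output is three log-rank p-values. Each compares the two strategies inside one centre, and none contrasts the centres. One significant and one non-significant result are not evidence that the two effects differ, because the gap between them may be well within chance.

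The trial is meant to guide implementation in Dutch burn care, which here means these three centres. A pattern in which LDI seems to work in one centre and not in another could be taken as a real difference between centres even if the true effect were the same in all three.

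**Working it through.** **Inputs from the Sample size section.** "A 2-sided test with an α level of 0.05", power 0.80, "an overall effect of 2.25 (57.5%* 5.3) days can be expected", "with a standard deviation of 5 days", and "indicates a required total sample size of 190 patients", raised to 200 for 5% dropout. There are three centres.

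**Assumptions.** Three equal centres, since the article gives no split. A comparison of means stands in for the log-rank test, as in the plan's own calculation. The three centres are independent.

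**The plan's own figure first.** n per arm = 2 × (1.96 + 0.84)² × 5² / 2.25² ≈ 78, so 156 in total (158 with a t-test), not 190. The dropout step does reproduce: 190 / 0.95 = 200. The printed product 57.5% × 5.3 is 3.05, whereas 42.5% × 5.3 is 2.25. These are separate matters; their effect on this point is shown below. With 190 patients, overall power for 2.25 days is 0.87.

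**Power within a centre.** 200 / 6 ≈ 33 per arm. A noncentral t calculation with difference 2.25 and SD 5 gives 0.437. The 95% CI half-width is t(64 df) × 5 × √(2/33) = 2.46 days, wider than the planned effect.

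**Three tests under one common effect of 2.25 days.**
- All three significant: 0.437³ = 0.08
- None significant: 0.563³ = 0.18
- Mixed: 1 − 0.437³ − 0.563³ = 0.74

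**Smaller common effects.** Here 190 / 6 = 31.7 per arm, SE = 5 × √(2/31.7) = 1.257 days, and power ≈ Φ(effect/SE − 1.96). The no-effect row uses the 5% level directly.

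| True effect in every centre | Power per centre | Mixed significance |
|---|---|---|
| 1.5 days | 0.222 | 1 − 0.222³ − 0.778³ = 0.52 |
| 1.0 day | 0.122 | 1 − 0.122³ − 0.878³ = 0.32 |
| 0 | 0.05 | 1 − 0.05³ − 0.95³ = 0.14 |

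On this basis the 2.25-day case gives power 0.433 and mixed results 0.74, so the choice between 190 and 200 patients hardly matters.

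**Reversed direction.** With a true effect of 2.25 days, one centre's estimate points the wrong way with probability Φ(−2.25/1.257) = 0.037. At least one of three does so with probability 1 − 0.963³ = 0.11.

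**Sensitivity.** Unequal splits from 40/35/25 to 70/15/15 give mixed results in 0.74 to 0.82 at 2.25 days. Taking the printed product of 3.05 days instead, the range over equal and unequal splits is 0.63 to 0.85. At a total of 156, power per centre is about 0.37 and mixed results occur about 70% of the time.

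**The alternative.** A 2-df interaction test at the 5% level would signal heterogeneity in 5% of trials under a common effect. Its power depends on λ = Σ(effect − mean effect)² / SE², with SE² = 1.579.
- True effects 1.125, 2.25 and 3.375 days: λ = 2.53 / 1.579 = 1.60, power 0.19
- True effects 0, 2.25 and 4.5 days: λ = 10.125 / 1.579 = 6.41, power 0.61
- One pairwise contrast at 80% power: 1.257 × √2 × (1.96 + 0.84) ≈ 5.0 days

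**The case against.** The text at issue is one sentence closing a paragraph of limitations. It names no test, no threshold and no rule for comparing p-values across centres. It is compatible with descriptive curves or estimates by centre, and an article may leave the details to a fuller plan. Centre-specific estimates with standard errors are in fact the inputs to a heterogeneity test.

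Part of this stands. A reader might infer that sub-analyses per centre can never show whether the effect differs. That holds only for separate p-values; estimates with CIs would allow an informal comparison. The article promises neither estimates nor a comparison, however. It also does more than stay silent: it raises the question and commits to a method that, as described, does not answer it.

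A reader might also infer that conflicting results are to be expected whatever the truth. The 74% requires a true common effect near 2.25 days, and the same Discussion expects a learning effect to shrink the difference. At 1.0 day, agreement on significance is the likelier outcome. Conflicting here means mixed significance, seldom opposite directions.

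Nothing in the article says that centre-specific decisions will follow, so that consequence is a risk and not a plan. The objection that the interaction test is weak is also correct. It limits what the fix can deliver, but it does not make separate tests an answer to the question.

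**Conclusion.** The point holds in a limited form. The plan expects the effect of LDI to vary by centre and names only sub-analyses per centre to study it. Separate within-centre tests do not test that variation. With equal centres, SD 5 and a comparison of means in place of the log-rank test, a common effect of 2.25 days gives mixed significance about 74% of the time. The figure is about 52% at 1.5 days, 32% at 1.0 day and 14% with no effect. The size of the problem therefore depends on the true effect; the mismatch between question and method does not.

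The documents do not support a claim that the trial's main conclusion is at risk. The primary comparison is overall, and the centre sub-analyses do not enter it.

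**What to change.** Replace the sentence in the Discussion with wording such as:

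> Differences between centres in the effect of LDI will be assessed by a strategy-by-centre interaction in a Cox model for time to wound healing, with strategy, centre and TBSA stratum as factors. Centre-specific effects will be shown with 95% CIs, descriptively, without centre-specific significance claims. A non-significant interaction will not be read as showing that the effect is the same in all centres.

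The Statistical analysis section has no regression model to extend, so the Cox model must be named there as a secondary analysis. The log-rank test stays as the primary analysis.

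The cost is one added secondary model, with no new data and no extra patients. The main drawback is low power: about 0.19 for true effects of roughly 1.1, 2.25 and 3.4 days, with a pairwise difference of about 5 days needed for 80%. These figures are on the scale of mean days and are only a guide to a Cox interaction. The plan should state this limit. A treatment-by-enrolment-order term, to look at the learning effect mentioned in the same section, is an optional extra.

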## Ethical considerations

This study has been approved by the Medical Research Ethics Committee of Rotterdam (NL37844.101.11).
